### Randomization and blinding

Participants are randomized in a 1:1 ratio using a computer-generated, site-stratified, block randomization schedule. The study capsule will be labeled with sequential randomization numbers, and each patient will be assigned the lowest number available at each participating center. All patients, care providers, and attending physicians will be blinded to treatment assignment until the study is completed. The duplicated blinding codes will be given to the main research institution and the manufacturer to keep, and the blinding codes cannot be broken during the trial.

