## Methods/design

### Study design

This study is registered in the Chinese Clinical Trials Registry (ChiCTR-IPR-14005475). It is a multicenter, double-blind, randomized, placebo-controlled clinical trial. This study complies with the principles of the Declaration of Helsinki and Good Clinical Practice guidelines. Written informed consent will be obtained from all patients prior to their participation in this study, and the recruited patients will be randomized to either the Xiyue capsule group or the placebo group. We will rigorously follow the Consolidated Standards of Reporting Trials (CONSORT) recommendations in reporting the results [17].

The trial will be conducted in 25 centers in China (see in ​Additional file 1). A total of 1100 participants will be recruited. After acquiring consent from the participants or their parents and/or legal guardians, the participants will be enrolled in the trial, which consists of a 1-week run-in period, a 24-week treatment period, and a 24-week follow-up period. An outline of the study procedures is illustrated in Fig. 1.

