### Withdrawal, dropout, and discontinuation

Participants can voluntarily withdraw at any time during the trial. Subjects who meet the inclusion criteria, fill out and sign the consent form, and successfully enter the randomized trial who fail to complete the observational period proposed in the trial, regardless of time and reasons, are considered as dropout cases. Reasons for withdrawal will be recorded in case report forms (CRFs), and the last data recorded for these participants will be included in the data analysis.

The trial can be terminated in the following circumstances: (1) occurrence of serious adverse events (AEs) related to the research medication, (2) the test drug is found to have no clinical value during the trial, (3) financial and management reasons, and/or (4) administrative authorities terminate the trial.

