### Adverse events

AEs are defined as negative or unintended clinical manifestations following the treatment. Patients will be asked to report to the investigators any abnormal reactions occurring at any time during the trial. In addition, investigators will collect information about abnormal reactions monthly. All details of related and unexpected AEs, such as time of occurrence, degree of AE, and suspected causes, will be recorded on CRFs. There is also a data safety monitoring board to oversee the trial.

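### The article forbids opening the blinding codes during the trial and makes no exception for one patient's medical emergency

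*Protocol article*

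**What the plan says.** Three statements under Randomization and blinding in the protocol article fix the rule.

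- Who is blinded, and for how long: "All patients, care providers, and attending physicians will be blinded to treatment assignment until the study is completed".
- Who holds the codes: "The duplicated blinding codes will be given to the main research institution and the manufacturer to keep".
- Whether they may be opened: "the blinding codes cannot be broken during the trial".

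The safety provisions are in other sections.

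- Withdrawal, dropout, and discontinuation gives as one ground for terminating the trial "occurrence of serious adverse events (AEs) related to the research medication".
- Adverse events says: "Patients will be asked to report to the investigators any abnormal reactions occurring at any time during the trial". It also has the suspected cause of an event entered on the case report form, and adds: "There is also a data safety monitoring board to oversee the trial".

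On scale, Study design says: "The trial will be conducted in 25 centers in China". Under Intervention, all patients also receive conventional treatment, which includes antiplatelet, lipid-lowering, antihypertensive or antidiabetic drugs.

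**The concern.** A double-blind trial normally keeps its codes closed but leaves a way to open one patient's code when that patient's care requires it. Here the ban is absolute. It has no qualifier, and the sentence on who stays blinded runs to the end of the study and names attending physicians.

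Patient safety is the main thing at stake. These patients take the study capsules on top of several other drugs, so a serious event may have more than one plausible cause. The physician handling it may want to know whether the patient is on Xinyue or placebo, and under the rule as printed cannot be told.

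A smaller matter is record-keeping. If a code were opened under pressure of events, that would breach the protocol, and the article describes no record of when or why it happened. Urgent revascularization is part of the primary outcome, and the decision to perform it involves clinical judgement, so the analysts should know which patients' physicians had learned the assignment.

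**Working it through.** No arithmetic applies: the point rests on a procedural rule and on no rate, effect size or sample size. The check is a reading of the relevant sections side by side.

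1. **Scope of the ban.** The rule covers patients, care providers and attending physicians. It lasts until the study is completed. The codes are with two holders, the lead institution and the maker of the capsules. The ban is worded for the codes as such, so it binds both holders. No exception is attached.

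2. **Search for an exception elsewhere.** The sections on withdrawal and discontinuation, adverse events, visits and procedures, data quality control, and statistical analysis contain no emergency opening of a code. The monitoring board is named, but no access to the codes and no part in opening one is described. Showing the board results by arm would still give the physician of a single patient no route.

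3. **Comparison with the safety provisions.**

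| Provision | What it covers | Does it need an individual code? |
|---|---|---|
| Termination for drug-related serious events | The trial as a whole | Not stated |
| Patients report reactions at any time | Notification | No |
| Suspected cause recorded | Documentation | No |

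   These provisions show that serious reactions are foreseen and may arise at any point. None of them says that one patient's code will be opened, so there is no word-for-word contradiction. The gap is that the plan foresees the event and bars one piece of information a physician might need in managing it.

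4. **Omission or stated rule?** There are two possibilities. If the full protocol contains an emergency route, the article's sentence misstates it. If it contains none, the sentence is accurate and the rule itself needs changing. The sponsor has something to correct in both cases.

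5. **Can one code be opened alone?** The capsules carry sequential randomization numbers, and each patient receives the lowest number available at the center. Opening one number therefore directly discloses one assignment. Allocation is in blocks within site, so an opened code could hint at its neighbours if the block size were known at the center. The article does not give the block size.

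6. **Effect on the analysis.** Statistical analysis places every randomized patient in the intention-to-treat population, analyses by allocated arm, and plans endpoint collection over the whole follow-up for everyone. Censoring at last contact applies to patients lost to follow-up. Opening a code therefore changes neither the analysis set nor the censoring.

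7. **Timing.** Trial status reports 452 enrolled, so 1100 − 452 = 648 were still to be recruited when the article was written. A change then could have covered them from entry, as well as enrolled patients still under observation.

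**The case against.** The strongest reply is that the sentence concerns custody of the master code list. On that reading it says who keeps the duplicate lists and that they stay sealed. Emergency codes for single patients would be a separate arrangement, which a journal article may leave to the full protocol. The reading is possible, but it does not fit the wording well. The ban is not confined to the master list, and the sentence before it keeps attending physicians blinded to the end of the study without qualification. A reader who follows the text would conclude that no opening is allowed.

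A second reply is that the termination clause is about ending the trial and the adverse-event section is about reporting, so neither contradicts the blinding rule. That stands. These sections show only that serious events are foreseen.

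A reader might also draw three stronger conclusions that the documents do not support.

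- **That both code copies are kept away from every site.** One holder is the lead institution, which may itself be one of the 25 centers. The list is in Additional file 1, which is not shown. The text mentions no copy for the other centers; no more than that can be said.
- **That an unblinded patient would be withdrawn and censored around the time of a serious event.** No section makes unblinding a reason for withdrawal, and the statistical section already keeps all randomized patients in the analysis.
- **That a number of affected patients can be given.** The article has no rate of emergencies, and any count would rest on an unsupported guess.

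**Conclusion.** The point holds as a defect in a stated rule. The article bars opening the codes during the trial, keeps attending physicians blinded to the end, and makes no exception for one patient's emergency. Followed literally, this works against patient safety in a trial that itself foresees drug-related serious events.

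Its size cannot be put in numbers. The rule applies to every participant, but the need to use an exception would arise case by case. The expected effect on the treatment comparison is small, because openings are individual and the intention-to-treat analysis is unaffected. The case for change is patient safety and a proper record of any opening. It does not rest on bias in the planned estimate.

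The conclusion assumes that the sentence means what it says. If the full protocol already provides an emergency route, the remaining fault is that the published text denies it.

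**What to change.** The sponsor should reconcile the blinding section with the two safety sections. A workable amendment would:

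- limit the ban to elective opening of codes and to unblinding of groups of patients;
- state that a single patient's code can be opened in a medical emergency, with the criteria left to the sponsor and the treating physician (none is proposed here);
- require each opening to be logged with its date and reason;
- confirm that the patient stays in follow-up and in the intention-to-treat analysis, as the statistical section already provides.

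If the full protocol already has such a route, the article's sentence should be corrected to match it.

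The cost is one or two sentences and a log. The downside is that a few patients may become unblinded; the log lets the analysts identify them.

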### Date entry and quality control of data

CRFs have been used for data entry, and data from all participating centers will be imported into the clinical data management system (http://www.xyedc.com/). To maintain the quality of the data, we will adopt valid measures to ensure information accuracy, integrity, and authenticity. First, computer logic checks will be run to identify items such as inconsistent dates, missing data, and questionable values. After that, the supervisor will perform source data verification to check the consistency of the original data. Queries may be issued by the supervisor and will be answered by the site investigators (see in the additional file 3). Second, manual checks will identify more complicated and less common errors. Third, the supervisor will conduct the site visit to compare the electronic database with the source documents. Identified errors will be solved to ensure the data quality. Fourth, the Data Coordination Center will be in charge of data validation.

### Sample size calculation

The sample size was calculated on the basis of expected reduction in cardiovascular events (cardiac death, all-cause mortality, reoccurrence of MI, and any form of revascularization). A previous study suggested that the incidence for all major clinical cardiovascular events combined at 1 year after interventional treatment of CHD is 12.8 % [20]. Therefore, the hypothesis of this study is to reduce the incidence of cardiovascular events to 7 % in the treatment group. Given a type I error rate of α = 0.05, a power of 80 % (type II error rate of β = 0.2), the sample size for one arm needs to be 447, resulting in *n* = 2 × 447 = 894 patients. Considering a dropout rate of 20 %, a total of 1097 patients needs to be allocated to reach the required number of patients for the efficacy analysis. For convenience of randomization, we decided to recruit 1100 patients. The formula used to calculate the sample size is as follows:$$ n=\frac{p_1\left(1-{p}_1\right)\kern0.5em +\kern0.5em {p}_2\left(1-{p}_2\right)}{{\left({p}_1-{p}_2\right)}^2}{\left(u{}_{\upalpha}+\kern0.5em u{}_{\upbeta}\right)}^2 $$$$ \mathrm{n}\approx 447\ \mathrm{patients}/\ \mathrm{group} $$

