#### Inclusion criteria

CHD was diagnosed according to the guidelines [2, 18]. All participants must have received successful PCI.The time window is within 1 year after PCI and the patient must be clinically stable, defined as follows:No progressive chest pain is present.The troponin value is within normal range or slightly elevated, but lower than the 99th percentile of the upper reference limit value.The participants must have a Canadian Cardiovascular Society classification of angina I to IIPatients are diagnosed as having a syndrome of deficiency of both Qi and Yin according to TCM standards [19].Patients must be aged 18–75 years.Patients must have a New York Heart Association cardiac functional class I–IIPatients are informed about the trial and voluntarily sign the consent form.

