### Outcomes and measures

The primary outcome is the time from randomization to the first occurrence of the major adverse cardiovascular event (MACE): cardiac death (any death unless an unequivocal noncardiac cause could be established), nonfatal MI (appearance of pathological Q waves that were absent at baseline or a total creatine kinase [CK] level more than two times the upper limit of normal [ULN] with presence of CK isoenzyme MB higher than the ULN), and urgent revascularization with either PCI or coronary artery bypass graft. The secondary outcome measures is the time from randomization to the first occurrence of, stroke, pulmonary embolism, and peripheral vascular events, as well as death due to any cause. Safety outcomes, which include a complete blood count, kidney and liver function tests, high-sensitivity C-reactive protein level, cardiac function index, blood lipid levels, Quality of Life Questionnaire (QLQ) score, 36-item Short Form Health Survey (SF-36) score, and TCM syndrome score will also be monitored periodically. All AEs will be followed from randomization to the end of the trial. Items to be measured and the time window of data collection are shown in Table 1.

**Table 1 Tab1:** Measurement items and points of data capture

	Screening	Treatment period			Follow-up period	
	Visit 1	Run-in period (visit 2)	12 weeks (visit 3)	24 weeks (visit 4)	12 weeks (visit 5)	24 weeks (visit 6)
Informed consent	X					
Inclusion/exclusion criteria		X				
Demographic data	X					
Medical history	X					
Concomitant medications	X					
Tongue and pulse condition in TCM	X	X	X	X	X	X
Vital signs	X	X	X	X	X	X
12-lead ECG	X			X		X
Complete blood count, urine and stool tests	X			X		X
Liver and renal function tests	X			X		X
Coagulation function test	X			X		X
Adverse event evaluation			X	X	X	X
Dispense drug		X	X	X	X	X
Primary endpoint			X	X	X	X
Secondary endpoint			X	X	X	X
Cardiac function	X			X		X
hs-CRP	X			X		X
Lipid panels	X			X		X
QLR score	X		X	X	X	X
SF-36 score	X		X	X	X	X
TCM syndrome score	X		X	X	X	X

*Abbreviations: ECG* electrocardiogram, *hs-CRP* high-sensitivity C-reactive protein, *SF36* 36-item Short Form Health Survey, *TCM* traditional Chinese medicine, *QLQ* quality of Life Questionnaire​

X represents the indicators tested in the specific time period

Coagulation function test: prothrombin time, activated partial thromboplastin time, fibrinogen, thrombin time

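### The 80% power is derived for a broader composite counted from the procedure, not for the primary MACE counted from randomization

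*Protocol article*

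**What the plan says.** Protocol article, Sample size calculation: the trial is sized on a reduction in cardiovascular events, listed as "cardiac death, all-cause mortality, reoccurrence of MI, and any form of revascularization". The control rate of 12.8% is described as "the incidence for all major clinical cardiovascular events combined at 1 year after interventional treatment of CHD". The target is 7% on treatment, with α = 0.05 and 80% power, giving 447 per arm. After an allowance for 20% dropout this becomes 1097, rounded to 1100.

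Protocol article, Outcomes and measures: "The primary outcome is the time from randomization to the first occurrence of the major adverse cardiovascular event (MACE"). Its components are "cardiac death (any death unless an unequivocal noncardiac cause could be established"), nonfatal MI, "and urgent revascularization with either PCI or coronary artery bypass graft". Death from any cause is placed among the secondary outcomes: "stroke, pulmonary embolism, and peripheral vascular events, as well as death due to any cause".

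Protocol article, Inclusion criteria: "The time window is within 1 year after PCI and the patient must be clinically stable".

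The Study design section gives 24 weeks of treatment and 24 weeks of follow-up, 48 weeks in all. The Statistical analysis section specifies an intention-to-treat population, censoring at last contact, a Cox model and two-sided tests.

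**The concern.** Two definitions and two clocks are printed in the same article. Each component of the sizing composite equals or contains its counterpart in the primary MACE, so the tested endpoint is, as worded, a subset of the one used for sizing. The 12.8% runs from the procedure. The primary outcome runs from randomization, in patients selected for stability who may already be months past PCI.

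Two differences probably lower the control rate most: only urgent revascularization counts, and patients enter stable and later. Despite this, 12.8% and 80% are carried over unchanged.

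The stated power is the justification for 1100 patients. If primary events are rarer than assumed, a neutral result could be read as adequately powered evidence of no benefit. The article states no event target that would reveal a shortfall.

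**Working it through.** **1. The plan's own figure.** Inputs from the Sample size calculation section: p1 = 0.128, p2 = 0.07, α = 0.05 (two-sided, from Statistical analysis), power 80%.

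- Printed formula: (0.128×0.872 + 0.07×0.93) / 0.058² × (1.960 + 0.842)² = 0.1767 / 0.003364 × 7.849 ≈ 412.3, so 413 per arm.
- With a continuity correction the result is 449, close to the stated 447. The gap between the printed formula and 447 is a separate matter.
- At 447 per arm without the correction, power is about 83%.

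The 80% is therefore about right for the rates that were put in. The question is whether those rates belong to the primary MACE.

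**2. The two endpoints side by side.**

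| | Sample size calculation | Outcomes and measures |
|---|---|---|
| Death | cardiac and all-cause | cardiac, by default unless clearly noncardiac |
| MI | recurrent | nonfatal |
| Revascularization | any form | urgent, PCI or bypass |
| Clock starts | at the intervention | at randomization, up to 1 year after PCI, patient stable |
| Duration | 1 year | 48 weeks |

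**3. The planned effect as a hazard ratio.** HR = ln(0.93)/ln(0.872) = 0.530, so |ln HR| = 0.635. Events needed for 80% power at two-sided 0.05 (Schoenfeld): 4 × (1.960 + 0.842)² / 0.635² = 77.8, so 78.

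**4. Power under the planned analysis.** All 550 per arm are analysed, and 20% are lost evenly over 48 weeks. A lost patient contributes on average about half the follow-up, so expected events are close to 550 × 0.9 × (pC + pT), where pC is the 48-week control rate and pT = 1 − (1 − pC)^0.530. Power = Φ(0.635 × √events / 2 − 1.96).

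| Control rate | Treated rate | Expected events | Power |
|---|---|---|---|
| 12.8% | 7.0% | 98 | 88% |
| 10% (assumed) | 5.4% | 76 | 79% |
| 8% (assumed) | 4.3% | 61 | 70% |
| 6% (assumed) | 3.2% | 46 | 57% |

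Expected events fall to 78 at a control rate of about 10%.

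**5. The 4 weeks alone.** At constant hazard, 1 − 0.872^(48/52) = 11.9% and 1 − 0.93^(48/52) = 6.5%. Expected events are about 91 and power is about 86%, so the shorter follow-up matters little by itself.

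**The case against.** A reader might infer that the trial is underpowered. The documents do not support that. They give no rate for the primary MACE, so the rates below 12.8% are assumptions. Several features also limit the gap:

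- **Death.** Any death without a clearly noncardiac cause counts as cardiac, which brings cardiac death close to all-cause death.
- **Revascularization.** Any form could mean PCI or bypass, not urgent or elective. The urgent restriction is likely to remove events, but the wording does not prove it.
- **Entry.** There is no minimum interval after PCI, so some stable patients may enrol early. How many early events are missed depends on entry times that are not given.
- **Source of 12.8%.** The figure comes from a cited study whose components are not shown. That it refers to the listed composite is read from the adjoining sentences.

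A harsher calculation is also tempting: drop 20% of patients and compare proportions in 440 per arm. With the planned risk ratio of 0.07/0.128 held, that gives 71%, 61% and 48% at control rates of 10%, 8% and 6%, with 80% power needing about 12.1%. It is not the planned analysis. The Cox model keeps all randomized patients and uses follow-up up to censoring, so there is more reserve than those figures suggest.

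These objections bear on the size of the loss. They do not remove the mismatch: the article sizes one endpoint, tests another, and offers no bridge.

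**Conclusion.** The point stands as a mismatch between the endpoint sized and the endpoint tested. The 80% is not a statement about the primary MACE. The MACE control rate is probably below 12.8%, mainly because only urgent revascularization counts and because patients enter stable and later.

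How much power is lost is unproven. On the planned analysis the control rate can fall from 12.8% to about 10% before power drops below 80%. This rests on a constant hazard ratio of 0.53 over the whole 48 weeks, 20% loss spread evenly, and 1:1 allocation of 1100 patients.

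**What to change.** In the Sample size calculation section:

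1. Restate the calculation for the primary MACE as defined in Outcomes and measures, over 48 weeks from randomization.
2. State the event requirement: 78 first MACE for a hazard ratio of 0.53 at two-sided 0.05 and 80% power.
3. Replace the single 80% figure with time-to-event power across control rates of 6% to 12%, with the loss assumption stated.
4. Keep the sample size at 1100.

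A blinded pooled event count may indicate which row applies. At a hazard ratio of 0.53, control rates of 10%, 8% and 6% correspond to pooled 48-week rates of about 7.7%, 6.2% and 4.6% (the mean of the two arms). Enrolment is still open with 452 entered, so the count must allow for incomplete follow-up and can only be indicative.

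The cost is a paragraph, a short table and, if used, one blinded count. It adds no patients, needs no unblinding and spends no alpha. The downside is that the stated power may become less favourable.

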### Statistical analysis

The data from all participating centers will be combined for statistical analysis of the primary and secondary endpoints as well as AEs. The analysis will be done at Beijing Jiaotong University. Continuous variables will be presented as the mean ± SD. The comparability of the characteristics between the two study groups will be assessed using a two-samples Student’s *t* test for continuous variables and the χ^2^ test or Wilcoxon test, when appropriate, for categorical variables. The Wilcoxon paired signed-rank test will be used for within-group comparisons.

All randomized patients constituted the intention-to-treat population. All participants will be analyzed according to their original treatment allocation. Primary and secondary endpoint data will be collected for the entire follow-up period for all patients. Patients lost to follow-up will be considered at risk until the date of last contact, at which point they will be censored. Kaplan-Meier curves will be used to examine MACE-free survival time. The Cox proportional hazards model with covariates of treatment will be used for primary and secondary analyses. Hazard ratios and 95 % confidence intervals for each of the categories determined by age, sex, diabetes, and conventional therapy will be provided for the primary and secondary endpoints.

For all analyses, a value of *P* < 0.05 will be considered statistically significant, and all tests will be two-tailed. All analyses will be conducted using SAS software version 9.2 (SAS Institute, Cary, NC, USA).

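### The sample-size figures do not agree with each other: the printed formula gives 413 per arm, not 447, and 894 evaluable patients at 20% dropout need 1118 allocated, not 1097

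*Protocol article*

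**What the plan says.** All the figures stand in the protocol article under Sample size calculation, except the sidedness and the allocation ratio.

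- Error rates: "Given a type I error rate of α = 0.05, a power of 80 % (type II error rate of β = 0.2". Under Statistical analysis, "all tests will be two-tailed".
- Control event rate, in per cent: "combined at 1 year after interventional treatment of CHD is 12.8".
- Target for the active arm: "reduce the incidence of cardiovascular events to 7 % in the treatment group".
- Allocation, under Randomization and blinding: "Participants are randomized in a 1:1 ratio".
- Result: "the sample size for one arm needs to be 447", doubled to 894.
- Dropout of 20%, after which "a total of 1097 patients needs to be allocated to reach the required number of patients for the efficacy analysis". This is rounded up to a recruitment target of 1100.

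The section closes by displaying the formula that it says was used. This is the unpooled two-proportion formula with no continuity term, followed directly by a result of about 447 per group.

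**The concern.** The formula, its inputs, the per-arm result, the dropout rate and the totals are printed together, so a reader can check every step. Two steps fail independently: formula to 447, and 894 to 1097.

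At stake is whether 1100 patients meet the plan's own requirement. The printed chain gives two answers. On the displayed formula 1100 is more than enough. On the stated requirement of 894 evaluable patients it falls short at the stated dropout. Recruitment was still open when the article was written, with 452 enrolled according to Trial status, so a clear statement of the requirement still had practical use.

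**Working it through.** **Inputs.** p1 = 0.128, p2 = 0.07, difference d = 0.058, 1:1 allocation, dropout 20%. Two-sided alpha 0.05 gives u_alpha = 1.95996; power 80% gives u_beta = 0.84162.

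**Step 1: the printed formula.** n = [p1(1−p1) + p2(1−p2)] / d² × (u_alpha + u_beta)²

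- Variance term: 0.128 × 0.872 + 0.07 × 0.93 = 0.111616 + 0.0651 = 0.176716
- d² = 0.003364
- (1.95996 + 0.84162)² = 7.8489
- n = 0.176716 / 0.003364 × 7.8489 = 412.3, so **413 per arm** and 826 in all

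The stated 447 is not reproduced; the gap is 34 per arm.

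**Step 2: can 447 be reached another way?**

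| Variant (12.8% v 7%) | n per arm |
|---|---|
| Printed formula, one-sided alpha, 80% power | 325 |
| Printed formula, two-sided, 85% power | 472 |
| Printed formula, one-sided, 90% power | 450 |
| Pooled-variance version, two-sided, 80% | 416 |
| Arcsine, two-sided, 80% | 408 |
| Pooled version with continuity correction | 449 |
| Printed formula with continuity correction | 446.1, so **447** |

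The last row uses n_c = (n/4) × [1 + √(1 + 4/(n·d))]² = (412.31/4) × [1 + √(1 + 4/23.914)]² = (412.31/4) × 2.0804² = 446.1.

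Of the variants tried with the stated rates, alpha and power, only this one gives 447. If the rates may move, the printed formula also gives 446.6 (447) at p2 = 7.2%, but the article states 7%.

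**Step 3: dropout.**

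- 894 / (1 − 0.20) = 1117.5, so **1118**
- Multiplying by 1.2 instead, a common slip: 894 × 1.2 = 1072.8, so 1073
- Neither is 1097. The dropout that 1097 implies is 1 − 894/1097 = 18.5%
- From the printed formula: 826 / 0.8 = 1032.5, so 1033

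**Step 4: what 1100 delivers.**

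- 1097 × 0.8 = 877.6 and 1100 × 0.8 = **880**, which is 14 short of 894
- Dropout that 1100 can absorb while keeping 894: 1 − 894/1100 = **18.7%**

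**Step 5: power with 440 evaluable per arm.**

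- Printed formula: d × √(440/0.176716) = 2.894; 2.894 − 1.960 = 0.934; power **82.5%**
- With continuity correction: effective n = 440 × [1 − 1/(440 × 0.058)]² = 406.2; d × √(406.2/0.176716) = 2.781; 2.781 − 1.960 = 0.821; power **79.4%**

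**The case against.** Four points can be made for the plan.

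1. *447 may be right.* The displayed formula with a standard continuity correction rounds up to exactly 447. If that was done, the requirement is valid and the only fault is a term missing from the equation. This stands as the likeliest explanation, though the article cannot confirm it. A reader might infer that the plan overstates its per-arm requirement by 34 patients (8%); the documents do not support that, because 34 is the gap between the figure and the formula as displayed, and the figure may be the correct one of the two.

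2. *The dropout slip is small.* 1118 − 1097 = 21 patients (1.9%), and 894 − 880 = 14 patients (1.6%). This stands.

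3. *Dropouts are not lost to the analysis.* Under Statistical analysis, all randomized patients are analysed, and those lost to follow-up count as at risk until last contact and are then censored in a Cox model. They still contribute time and any earlier events, so treating 880 as the whole information is pessimistic. This stands, and it defeats the stronger inference that the trial is underpowered. It does not rescue the text, which presents 1097 as the number that secures the efficacy analysis at 20% dropout.

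4. *An article condenses.* This does not help here. Nothing is missing that a fuller document would supply; the printed figures contradict each other.

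A reader might also want an event target because the analysis is a Cox model. Sizing from one-year proportions is a common choice, and an event count may be left to a fuller document, so this is not part of the point.

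**Conclusion.** The inconsistency is real and definite. As printed, the formula and inputs give 413 per arm, not 447, and 894 at 20% dropout gives 1118, not 1097. On the plan's own requirement, 1100 is 18 short of the 1118 to be allocated and 14 short of the 894 to be evaluable.

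The consequence is small. Counting completers only, power is about 82.5% or 79.4%, depending on whether the continuity correction belongs to the calculation. The worse figure is 0.6 percentage points below the stated 80%. Both rest on the planned rates of 12.8% and 7% and on two-sided testing at 5%.

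This is a wrong stated figure that should be corrected. The documents do not support reading it as a failure of design or as a reason to change the recruitment target.

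**What to change.** Print one chain that reproduces, keeping the target at 1100. Which one applies depends on the calculation that was actually done, which the authors can check.

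- **(a) Keep the displayed formula.** Restate 413 per arm, 826 evaluable and 1033 allocated at 20% dropout. Add that 1100 leaves 880 evaluable at that dropout, with about 82.5% power.
- **(b) Show the continuity-corrected formula.** Keep 447 and 894, change 1097 to 1118, and state that 1100 tolerates 18.7% dropout, or gives about 79.4% power if dropout reaches 20%.

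If 447 came from some other input, such as an unrounded event rate, print that input; the correction from 1097 to 1118 is then still needed.

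The cost is a few lines of text. Recruitment, randomization and analysis do not change.
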